**Methods/Design:**

This is a mixed (retrospective and prospective) longitudinal observational study enrolling 90 patients who will be recruited from a reference center for CD in Brazil. Patients with CCC receiving AMIO will be compared with those not receiving the drug. AMIO was prescribed at the discretion of the treating physician, independently of the present study. Eligible participants will be invited to participate during routine medical appointments. Clinical data, including electrocardiographic and echocardiographic parameters obtained during routine follow-up, will be retrospectively extracted from medical records. Blood samples will be collected at predetermined time points. The primary endpoint will be the inflammatory profile and serological reactivity to anti-*T. cruzi* in CCC patients. Secondary endpoints will include: (**1**) cardiovascular events; (**2**) CCC progression; (**3**) implantable cardioverter-defibrillator (ICD) implantation; (**4**) heart transplantation; (**5**) all-cause death and (**6**) a composite endpoint. The association between AMIO use and longitudinal changes in continuous variables will be determined using mixed linear models. Cox regression analysis will be used to investigate the relationship between AMIO use and selected outcomes (cardiovascular events, CCC progression, and death), adjusted for potential confounders. Hazard ratios (HRs) with 95% confidence intervals (CIs) will be reported.

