### Study design

This is a mixed (retrospective and prospective) longitudinal observational study designed to evaluate the association between chronic use of amiodarone (AMIO) and the following:

(I)**Primary outcome:** inflammatory profile, serologic reactivity to anti-*T. cruzi* antibody, and parasitic load;(II)**Secondary outcomes:** cardiovascular events (new sustained atrial arrhythmias, new sustained or non-sustained ventricular tachyarrhythmias, stroke, heart failure, atrioventricular block, and cardiovascular hospital admissions), CCC progression, internal cardioverter-defibrillator (ICD) implantation, heart transplantation, all-cause death, and a composite endpoint (including the aforementioned cardiovascular events, disease progression, ICD implantation, heart transplantation, and death).

Patients with CCC who take AMIO (exposed group) will be compared with those who do not take this drug (non-exposed group). To minimize potential confounding, patients will be matched based on the stage of CCC according to the Brazilian Consensus on Chagas Disease (A and B1 *versus* B2 and C), age (<50 years *versus* >50 years), and sex (female *versus* male) [15].

Clinical and laboratory data including blood tests, ECG, transthoracic two-dimensional echocardiography (ECHO), and 24-hour Holter monitoring, will be evaluated at three different time points:

(i)**Retrospective data**: from up to 3 years before the start of the study;(ii)**Baseline/recruitment**: at the time of inclusion in the study;(iii)**Prospective data**: during the 2 years of follow-up after recruitment;

The duration of the study, totaling five years of clinical follow-up, was established considering the CCC progresses at a rate of approximately 2% per year [22]. At recruitment, blood samples will be collected for biochemical and molecular analyses to obtain information related to the study’s primary outcome (Table 1) (Fig 1).

**Table 1 pone.0347305.t001:** AMIO-CHAGAS’s study Chronogram: Enrollment, Interventions and Outcome Assessments.

			Retrospective data	Recruitment	Prospective data
			2020 −2022	2023 - 2025	2025 - 2027
**Primary outcome:**	**Immunomodulatory effect**	Gene expression of CCC progression biomarkers in PBMCs	**–**	**x**	**–**
		Determination of serum levels of cytokines and nitric oxide	**–**	**x**	**–**
	**Trypanocidal effect**	Determination of anti-*T. cruzi* antibody titers	**–**	**x**	**–**
		*T. cruzi*-antigen quantification	**–**	**x**	**–**

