### Study population

Participant recruitment began on March 7, 2023, and is expected to be completed by December 2025. Participants are being recruited sequentially during their routine medical visits. Patients using AMIO are identified from the database of individuals monitored by the Clinical Research Laboratory on Chagas Disease at INI-Fiocruz. Only patients who have been receiving AMIO for at least three months will be included, ensuring adequate tissue impregnation with a cumulative dose of 10 g [23].

Inclusion criteria are as follows:

Confirmed diagnosis of CD, based on two serological tests with different methodologies (enzyme-linked immunosorbent assay [ELISA] and chemiluminescence) [14,15];Individuals over 18 years of age;Patients classified within the following CCC stages: A, B1, B2, and C [15].

Exclusion criteria are as follows:

Co-infection (HIV, hepatitis B and C, HTLV, Hansen’s disease, leishmaniasis and paracoccidioidomycosis);Immunosuppression of any nature;Cancer;Patients with stage D of CCC will be excluded due to their complex clinical management, including frequent hospitalizations and medication adjustments, which could affect the study’s feasibility.

Patients meeting the inclusion criteria will be invited to participate in the study, and written informed consent will be obtained from all individuals who agree to enroll.

Importantly, AMIO use was prescribed at medical discretion to treat atrial or ventricular arrhythmias [12], independently of this study, characterizing an observational study design.

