### Sample size

A minimum sample size of 90 volunteers was estimated, with 45 using AMIO and 45 not using AMIO. The sample size calculation for the primary endpoint was based on a study by Rodriguez-Angulo et al., 2017 [26] which evaluated differences in inflammatory markers in individuals with CD treated with AMIO (IFN-γ: 43.75 ± 24.83; TNF-α: 27.08 ± 13.81) compared to untreated individuals (IFN-γ: 84.37 ± 35.08; TNF-α: 52.08 ± 23.38). For the secondary endpoint, sample size calculation was based on a study by Saraiva et al., 2022 [22], which compared LVEF at different stages of CCC (LVEV; Stage A: 68.0 ± 6.4; Stage B: 54.7 ± 9.1; Stage C: 36.7 ± 10.7). Sample size calculations assumed a two-sided significance level of α = 0.05, a statistical power of 80% (1 − β = 0.8), and standard deviations and mean differences derived from these studies. The largest sample requirement among the two endpoints was adopted, and the sample size was increased by 20% to account for potential losses or refusals, resulting in a total of 90 participants.

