### Statistical analysis

Descriptive statistics were used to summarize the characteristics of the study population. Continuous variables will be presented as medians and interquartile ranges (IQR), and categorical variables as absolute and relative frequencies. Missing data will be assessed for their pattern and mechanism (i.e., missing completely at random (MCAR), missing at random (MAR), or missing not at random (MNAR)). The primary approach to handling missing data will be determined once the dataset is available. Depending on the extent and nature of missingness, appropriate strategies may include multiple imputation, complete case analysis, or sensitivity analyses to evaluate the robustness of the findings. The Shapiro-Wilk test will be used to assess the normality of continuous variables. When distributions deviate from normality, appropriate transformations or non-parametric tests will be applied.

Comparisons of patient characteristics according to AMIO use will be evaluated using the independent Student’s t-test for normally distributed continuous variables or the Mann-Whitney U-test for non-normally distributed data. Categorical variables will be compared using the chi-square test or Fisher’s exact test, as appropriate. Correlations between continuous variables related to the primary outcome will be assessed using Pearson or Spearman correlation coefficients, depending on data distribution. AMIO use and longitudinal changes in continuous variables will be analyzed using mixed linear models, adjusted for the duration of amiodarone use. Analyses of time course outcomes (e.g., cardiovascular events, disease progression, all-cause mortality) will be conducted using Cox proportional hazards regression models adjusted for potential confounders such as age, sex, comorbidities and previous etiologic treatment. Hazard ratios (HRs) and their 95% confidence intervals (CI) will be reported. A two-sided p-value ≤ 0.05 will be considered statistically significant.

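### The mixed models adjust AMIO use for duration of AMIO use, which is part of the exposure, so the AMIO main effect becomes a contrast at zero duration

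*Protocol article*

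**What the plan says.** Four statements in the protocol article bear on this.

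- Abstract, Methods/Design, on the purpose of the model: "The association between AMIO use and longitudinal changes in continuous variables will be determined using mixed linear models".
- Study design, on the contrast: "Patients with CCC who take AMIO (exposed group) will be compared with those who do not take this drug (non-exposed group".
- Study population, on entry of users: "Only patients who have been receiving AMIO for at least three months will be included".
- Statistical analysis, on the adjustment: "AMIO use and longitudinal changes in continuous variables will be analyzed using mixed linear models, adjusted for the duration of amiodarone use".

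The next sentence of the Statistical analysis section gives the Cox models a different set: "adjusted for potential confounders such as age, sex, comorbidities and previous etiologic treatment". Duration of AMIO is not in that list. The article does not say whether duration in the mixed model is fixed at baseline or updated, centred, or limited to users.

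**The concern.** Adjustment is meant to remove differences between groups that are not due to the exposure. Duration of AMIO is a feature of the exposure itself and has no variation among never-users. Entered beside the AMIO indicator, it does not make the groups more comparable; it changes what the AMIO coefficient means. A reader would take that coefficient as the difference between users and non-users. It would instead be the fitted difference for a user with no accumulated exposure, a value below the three-month minimum that the article sets at inclusion.

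At stake is the reading of the repeatedly measured continuous outcomes: LVEF, ventricular volumes, strain and ECG intervals. A real average difference could be reported as small or absent, or estimated with needless imprecision.

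**Working it through.** **Inputs.** From the article: "A minimum sample size of 90 volunteers was estimated, with 45 using AMIO and 45 not using AMIO", two-sided alpha 0.05, and at least three months (0.25 years) of AMIO in users at inclusion. The article gives no figure for this analysis that could be reproduced, and no distribution of durations.

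Assumed: durations uniform from 0.25 to 3, 6 or 10 years, or 0.25 plus a lognormal (median 3 years, log-SD 0.7); outcome SD 1; true average difference Δ = −0.60 SD. With 45 per group the difference detectable at 80% power is (1.96 + 0.84) × √(2/45) = 0.59 SD, so −0.60 is about the smallest effect the study could find reliably.

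**Step 1: meaning of the AMIO main effect.** In E[y] = b0 + b1·AMIO + b2·duration, with duration 0 in non-users and mean m in users, b1 = Δ − b2·m. This is algebra and needs no simulation. For durations uniform from 0.25 to 10 years, m = (0.25 + 10)/2 = 5.125.

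- Effect proportional to duration: b2 = −0.60/5.125 = −0.117 per year, so b1 = −0.60 + 0.117 × 5.125 = 0.00.
- Half of the effect follows duration: b1 = −0.60 + 0.30 = −0.30.
- Duration has no effect: b1 = −0.60.

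**Step 2: precision of the main effect.** Without duration, Var(b1) = 2σ²/n. With it, Var(b1) = 2σ²/n + σ²m²/(n·s²), where s² is the variance of duration among users. The SE ratio is √(1 + m²/(2s²)).

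| Longest duration | m | s² | SE ratio |
|---|---|---|---|
| 3 years | 1.625 | 2.75²/12 = 0.630 | √3.10 = 1.76 |
| 6 years | 3.125 | 5.75²/12 = 2.755 | √2.77 = 1.67 |
| 10 years | 5.125 | 9.75²/12 = 7.922 | √2.66 = 1.63 |

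**Step 3: simulation of steps 1 and 2.** 4000 cross-sectional data sets per scenario, with ranges over the 10-year uniform and the lognormal durations:

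| True pattern | AMIO coefficient, no duration | Rejection rate | AMIO coefficient, with duration | Rejection rate |
|---|---|---|---|---|
| Proportional to duration | −0.60 | 76–78% | 0.00 | 4–5% |
| Half follows duration | −0.60 | 79–80% | −0.30 | 14–17% |
| Unrelated to duration | −0.60 | 81% | −0.60 | 41–50% |

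In the last row the SE rises from 0.210 to 0.305–0.346, a ratio of 1.45–1.65. With duration centred within users and set to 0 in non-users, the coefficient is −0.60 in every row, with 79–81% power.

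**Step 4: mixed model.** Random intercept, three annual visits, level effect proportional to baseline duration (10-year uniform), and a true extra slope of −0.30 per year in users; 100 data sets.

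| Duration term | AMIO (SE) | AMIO × time (SE) |
|---|---|---|
| None | −0.61 (0.211) | −0.30 (0.089) |
| Baseline, main effect only | −0.04 (0.318) | −0.30 (0.089) |
| Centred within users | −0.61 (0.206) | −0.30 (0.089) |
| Updated at each visit | −0.04 (0.318) | −0.19 (0.101) |

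The last row follows from the algebra. Updated duration is baseline duration plus time, so AMIO × time loses the per-year duration coefficient: −0.30 + 0.117 = −0.18.

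**Step 5: six annual visits** (3 years back to 2 years forward, 45 per group, random intercept). Baseline duration as a main effect leaves AMIO × time and its SE (about 0.03) unchanged. Duration updated at each visit raises that SE to about 0.05–0.07, roughly 1.6 to 2.2 times, and takes AMIO × time to about zero when the effect accrues with duration. The SE ratio depends on the visit schedule: in step 4, with three visits, it is 0.101/0.089 = 1.13.

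**The case against.** The strongest reply is that the sentence is about longitudinal change, where the natural quantity is AMIO × time and not the main effect. Steps 4 and 5 bear this out: baseline duration as a main effect does that term no harm. A reader might infer that the AMIO effect is null by construction. The article does not support that. It holds for the main effect only if the effect is strictly proportional to duration, and for AMIO × time only if duration is also updated at each visit. No section hypothesises proportionality; the three-month rule is justified by tissue impregnation, which reads more like a threshold.

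Three further objections stand in part.

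- The three-month minimum applies at inclusion. Retrospective data reach back up to 3 years, so some users may have visits before AMIO, and zero duration may be observed and not purely extrapolated. A coefficient anchored on those visits would still describe pre-treatment differences between the groups, not the drug.
- The article does not say whether former users may be controls. A few non-zero values there would not restore the average contrast.
- The coding of duration may be set out in a fuller plan, and centring within users would remove the difficulty. But the article states the adjustment without that qualification.

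That the Cox confounders are not repeated for the mixed model is not held against the plan; an article may leave that to the full document.

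**Conclusion.** The point holds in a limited form. The article states a rule that adjusts an exposure for one of its own components. The AMIO main effect then answers a different question from the users-versus-non-users one that the article poses. It is attenuated in proportion to how far the effect follows duration, and its SE is about 1.5 to 1.8 times larger under the assumed durations. AMIO × time is safe under one reading of the sentence (baseline duration, main effect only) and not under another (updated duration).

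The definition of the coefficient is certain for uncentred duration. The sizes rest on the assumed durations, visit schedule and variance components, which the article does not give.

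A reader might also infer that the primary endpoint is compromised. It is not: Table 1 places the cytokines, nitric oxide, gene expression, antibody and parasite measures at recruitment only, so they have no longitudinal change to model. The Cox analyses do not list duration. The affected outcomes are the repeated echocardiographic and ECG measures.

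**What to change.** Remove duration of AMIO from the main mixed model. Fit AMIO, time and AMIO × time with a patient random effect, adjusted for the confounders already named for the Cox models and for the matching factors (stage, age, sex). State which coefficient answers the question.

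Examine duration in a separate dose-response model among users. If it is to stay in the joint model, centre it within users, set it to 0 in non-users, and say so.

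The cost is one sentence of analysis text and one extra model, with no change to recruitment or data collection.

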## Abstract

**Background:**

Chronic Chagas cardiomyopathy (CCC) is the most significant clinical manifestation of Chagas disease (CD) due to its impact on morbidity and mortality. Cardiac manifestations include dilated cardiomyopathy, with ventricular dysfunction, heart failure, cardiac arrhythmias and cardioembolic events. Amiodarone (AMIO) is the most commonly used antiarrhythmic drug in CCC primarily prescribed for patients with severe conduction system abnormalities. Despite preliminary evidence, no clinical study has specifically evaluated the immunomodulatory and trypanocidal effects of AMIO in patients with CCC. The main objective is to evaluate the association of AMIO therapy with serological reactivity to anti-*T. cruzi* and the inflammatory profile of patients with CCC.

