**Discussion:**

Given the limited literature on the potential trypanocidal and immunomodulatory effects of AMIO in CCC, the findings of this study may provide new insights into the therapeutic potential of AMIO beyond its established antiarrhythmic properties.

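### The arrhythmia for which amiodarone is prescribed, and LVEF, are in neither the matching factors nor the named Cox covariates, and stage is controlled only in two broad groups

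*Protocol article*

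**What the plan says.** All references are to the protocol article.

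- **Exposure.** Study population: "AMIO use was prescribed at medical discretion to treat atrial or ventricular arrhythmias". The Abstract words the indication differently, as a drug "primarily prescribed for patients with severe conduction system abnormalities". Users must have taken AMIO for at least three months before inclusion.
- **Comparator.** Patients with stages A to C who do not take AMIO. The eligibility criteria do not ask for an arrhythmia.
- **Matching.** Study design: "patients will be matched based on the stage of CCC according to the Brazilian Consensus on Chagas Disease", in two groups ("A and B1 *versus* B2 and C"), and also on age, split at 50 years, and sex.
- **Model.** Statistical analysis: "Cox proportional hazards regression models adjusted for potential confounders such as age, sex, comorbidities and previous etiologic treatment".
- **Outcomes analysed by Cox regression.** Cardiovascular events, disease progression and death are given as examples. The cardiovascular events include new atrial and ventricular arrhythmias and atrioventricular block.
- **Available data.** ECG, 24-hour Holter and echocardiography with LVEF are done annually. Clinical records reach back up to three years before the study. The section on these tests says that Holter is used to find arrhythmias that predict death.

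**The concern.** By the protocol's own account, arrhythmia is both the reason for exposure and a predictor of outcome. That makes it the leading candidate confounder for AMIO against event risk. Neither design nor model addresses it by name: the comparator is not restricted to patients with arrhythmia, the match does not use it, and the stated covariates do not mention it. Ventricular function has the same gap, except so far as a two-level stage match captures it.

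If the Cox models are fitted with the named covariates, the hazard ratio compares patients who had a reason to be treated with patients who may not have had one. A raised hazard ratio could then reflect the prescribing decision, and a real association could be masked. The estimate would be hard to read in either direction.

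**Working it through.** **1. Which prognostic factors are controlled, and where**

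| Factor | Matched | Named in Cox model | Collected |
|---|---|---|---|
| Age | yes, split at 50 | yes | yes |
| Sex | yes | yes | yes |
| Stage | yes, A+B1 against B2+C | no | yes |
| LVEF | no | no | yes |
| Atrial or ventricular arrhythmia | no | no | yes |
| Comorbidities (undefined) | no | yes | not itemised |
| Previous etiologic treatment | no | yes | not itemised |

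Two of the four named covariates, age and sex, are already matching factors. The indication appears in neither control column. The same holds if the indication is taken as conduction abnormality, as the Abstract words it.

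**2. How much LVEF variation a two-level stage match can leave**

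The Sample size section gives mean LVEF by stage as "Stage A: 68.0 ± 6.4; Stage B: 54.7 ± 9.1; Stage C: 36.7 ± 10.7". The gaps are 68.0 − 54.7 = 13.3 points (A to B) and 54.7 − 36.7 = 18.0 points (B to C). These are gaps to stage B as a whole. The matching groups split B into B1 and B2, whose LVEF is not reported separately, so 13.3 and 18.0 are not within-group gaps. As a rough guide only, use the pooled B mean for both and assume that the stage mix differs by 20 percentage points between users and non-users:

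- A+B1: 0.20 × 13.3 = 2.7 points
- B2+C: 0.20 × 18.0 = 3.6 points

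If B1 patients have higher LVEF than B2 patients, which is plausible but not stated, both figures shrink. The stage SDs are 6.4 to 10.7, so this residual imbalance is modest.

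**3. Size of bias from uncontrolled arrhythmia (all inputs assumed)**

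The document gives neither the prevalence of arrhythmia by group nor its hazard ratio. For a binary confounder with prevalence p1 in users and p0 in non-users and hazard ratio h, the usual approximation to the apparent hazard ratio when AMIO has no effect is

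[1 + p1(h − 1)] / [1 + p0(h − 1)]

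| p1, p0 | h = 1.5 | h = 2 | h = 3 | h = 4 |
|---|---|---|---|---|
| 1.0, 0.1 | 1.43 | 1.82 | 2.50 | 3.08 |
| 1.0, 0.3 | 1.30 | 1.54 | 1.88 | 2.11 |
| 1.0, 0.5 | 1.20 | 1.33 | 1.50 | 1.60 |
| 0.6, 0.4 | 1.08 | 1.14 | 1.22 | 1.27 |

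For example, p1 = 1.0, p0 = 0.3 and h = 2 give 2.0/1.3 = 1.54. The spread, from 1.08 to 3.08, shows that the answer depends on inputs that the document does not supply.

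**4. How many covariates the data can carry**

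Study design gives progression of about 2% per year. With 90 patients:

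- two years: 90 × (1 − 0.98²) = 3.6 events
- five years: 90 × (1 − 0.98⁵) = 8.7 events, about 9

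A progression model cannot support a long list of separate covariates. Expected numbers for the other outcomes are not given.

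**The case against.** **The covariate list is only illustrative.** This stands in part. The named covariates are given as examples, comorbidities are undefined, and a condensed article may leave the final set to a fuller plan. A reader might infer that the plan excludes arrhythmia, LVEF and stage from the models. It does not; it fails to name them. The point survives because the comparator's eligibility and the matching factors are stated without any such openness, and a later plan cannot change who was enrolled. Naming general confounders but not the indication also points the analyst to the wrong set.

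**Stage is matched.** It is, and with 90 patients and three matching factors broad groups are understandable. A reader might infer from the published LVEF means that matched patients differ by 13 or 18 points. The document does not support that, for the reason given under the second calculation. What remains is that LVEF within a group is uncontrolled, and that stage matching does not balance arrhythmia directly.

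**The direction of bias is not certain.** This stands. Confounding by indication would be expected to act against AMIO. But users enter only after at least three months on the drug, and this survivor selection may act in its favour.

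**The composite.** A reader might infer that, because the composite contains arrhythmias and atrioventricular block, it is being used to show "the therapeutic potential of AMIO beyond its established antiarrhythmic properties". The protocol does not make that link. The Abstract's statement follows a reference to trypanocidal and immunomodulatory effects, which are the biomarker outcomes. A composite without those components is useful as a sensitivity analysis, not as the correction of an error.

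**Conclusion.** The point holds in a limited form. The indication for AMIO is prognostic by the protocol's own account, and neither the comparator definition, the match nor the named Cox covariates control it. LVEF is in neither list, and stage is controlled in two groups only. Fitted with the named set, the secondary-outcome hazard ratios would carry confounding by indication.

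No single bias figure should be quoted as a finding. A reader might take a spurious hazard ratio of 1.5 to 1.9 from the middle of the table, but that rests wholly on assumed prevalences and an assumed effect of arrhythmia.

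Severity is should-fix rather than must-fix. The Cox outcomes are secondary, the study describes itself as exploratory and speaks of association, and the progression hazard ratio will be imprecise whatever the covariates.

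**What to change.** In Statistical analysis:

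1. Name prior atrial or ventricular arrhythmia (ECG or Holter), LVEF as a continuous variable and four-level stage (A, B1, B2, C) as confounders for the Cox models, beside those already listed. State how the matching factors are accounted for, for example by stratifying on the matching groups.
2. Take these values from before AMIO start where the retrospective records allow. Otherwise flag that values at recruitment may already reflect the drug.
3. Enter the confounders through a propensity score or a penalised model rather than as a long covariate list, and report overlap between the groups.
4. As sensitivity analyses only, compare users with non-users who have a documented arrhythmia, and report the composite without its arrhythmia and atrioventricular-block components.

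**Cost.** The tests are already performed, so most of this is wording, but it is not free. Intervals will widen. If nearly all users and few non-users have an arrhythmia, propensity overlap will be poor. The restricted comparator may be small: at an assumed 25% prevalence, 0.25 × 45 leaves about 11 non-users. Records reach back at most three years, so pre-AMIO values will be incomplete for long-term users. The composite without those components will have fewer events.

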### Determination of serum levels of cytokines and nitric oxide

In addition to gene expression analysis of inflammatory markers in PBMCs, quantification of cytokine levels and nitric oxide in the serum of patients with chronic Chagasic cardiomyopathy (CCC) has previously been associated with the progression of symptomatic forms of the disease [26]. Accordingly, detection of IL-2, IL-17, IL-4, IL-6, IL-10, TNF, and IFN-ɣ will be performed using the Cytometric Bead Array Human Th1/Th2/Th17 kit (Becton Dickinson), following the manufacturer’s protocol. Furthermore, nitrate and nitrite concentrations will be quantified in patient serum samples using the Griess reaction (Sigma-Aldrich), according to the manufacturer’s specifications.

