**Continuous variables included:**

(i)Gene expression levels of TNF, IFN-γ, IL-10, TGF-β, iNOS, and NF-κB in PBMCs, quantified by RT-qPCR and expressed as fold change (arbitrary units);(ii)Serum cytokine concentrations—including IL-2, IL-4, IL-6, IL-10, IL-17, TNF, and IFN-γ—quantified in pg/mL using a Cytometric Bead Array (CBA);(iii)Serum levels of nitrate and nitrite (μM), determined by the Griess reaction;(iv)Anti-*Trypanosoma cruzi* IgG antibody titers, quantified by ELISA and reported as absorbance values;(v)Parasitic DNA load (parasite equivalents/mL), quantified by duplex TaqMan qPCR using the NAT Chagas kit;(vi)Left ventricular systolic ejection fraction (LVEF, %), as well as left ventricular diastolic and systolic volumes (mL), quantified using Simpson’s biplane method of discs via two-dimensional transthoracic echocardiography;(vii)Left ventricular diastolic function (graded by established echocardiographic criteria), right ventricular (RV) systolic function (expressed as fractional area change or TAPSE in mm), and strain parameters (%) of the left atrium (LA), right ventricle (RV), and left ventricle (LV), evaluated to provide a comprehensive assessment of cardiac mechanics;(viii)Electrocardiographic parameters: heart rate (beats per minute, BPM) and electrocardiographic intervals, including PR interval (ms), QRS duration (ms), QT interval (ms), and corrected QT interval (QTc, ms);(ix)Systolic and diastolic blood pressure (mmHg), measured on the left arm with participants seated in a quiet room after 5 minutes of rest, using an Omron digital sphygmomanometer;

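### Sixteen or seventeen unranked primary markers share one unadjusted 0.05 threshold, so the chance of a false primary finding can be far above 5%, mainly in the inflammatory panel

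*Protocol article*

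**What the plan says.** The Study design section gives a single primary outcome with three parts and no ranking: "inflammatory profile, serologic reactivity to anti-*T. cruzi* antibody, and parasitic load". Table 1 groups the measures under two headings, an immunomodulatory effect and a trypanocidal effect, all taken at recruitment only. The data-collection list itemises them:

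- six transcripts: "Gene expression levels of TNF, IFN-γ, IL-10, TGF-β, iNOS, and NF-κB in PBMCs";
- seven serum cytokines: "IL-2, IL-4, IL-6, IL-10, IL-17, TNF, and IFN-γ";
- serum nitrate and nitrite;
- anti-*T. cruzi* antibody absorbance;
- parasite DNA load.

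The abstract is narrower. It reads "The primary endpoint will be the inflammatory profile and serological reactivity to anti" *T. cruzi*, and parasitic load is absent.

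The Sample size section sizes the primary endpoint on IFN-γ and TNF-α alone, at "a two-sided significance level of α = 0.05, a statistical power of 80"%. The Statistical analysis section closes with "A two-sided p-value ≤ 0.05 will be considered statistically significant". It mentions no lead marker, order of testing or adjustment. The word exploratory appears once, in the last paragraph of the Discussion.

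**The concern.** The study asks whether amiodarone has immunomodulatory or trypanocidal effects in patients. As the rules stand, nothing prevents any one of the 16 markers with p ≤ 0.05 from being reported as a positive primary result. The 5% that a reader would attach to that result applies to one test, not to the best of 16. The two markers behind the sample size have no special standing in the analysis. Readers of the abstract and of the design section would also disagree on whether parasite load, the most direct trypanocidal measure, is primary.

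**Working it through.** **Plan's own figure.** The article states no family-wise error rate, so there is none to reproduce. The stated 90 participants (45 per group) is taken as given below. It does not follow from the cited inputs, which need far fewer, but that is a separate matter and does not affect this calculation.

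**Count of primary markers.**
- Immunomodulatory: 6 transcripts + 7 cytokines + 1 nitrate/nitrite = 14 (15 if nitrate and nitrite are separate).
- Trypanocidal: antibody + parasite load = 2.
- Total: 16 (17).

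**False-finding rate, no true effects, independent tests.** P(at least one) = 1 − 0.95^m.

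| Tests | Chance of at least one p ≤ 0.05 |
|---|---|
| 17 | 58.2% |
| 16 | 56.0% |
| 14 (inflammatory panel) | 51.2% |
| 2 (trypanocidal) | 9.75% |

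**Effect of correlation.** The article gives no correlations, so the values here are assumptions. With a common correlation ρ between test statistics (equicorrelated normal model):

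| ρ | 16 tests | 14 tests |
|---|---|---|
| 0 | 56.0% | 51.2% |
| 0.3 | 47.6% | 43.8% |
| 0.5 | 37.4% | 34.8% |
| 0.7 | 26.4% | 24.9% |
| 0.9 | 14.6% | 14.1% |

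Simulated t-tests on 45 versus 45 with 16 markers agree: 55.4% at ρ = 0, 47.9% at 0.3 and 38.1% at 0.5. For 16 tests the rate drops below 50% at ρ of about 0.24.

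**Cost of control for the planned effects.** Inputs are from the Sample size section; the SD is the root mean square of the two groups.
- IFN-γ: difference 84.37 − 43.75 = 40.62; SD = √((24.83² + 35.08²)/2) = 30.39; d = 1.34.
- TNF-α: difference 52.08 − 27.08 = 25.00; SD = √((13.81² + 23.38²)/2) = 19.20; d = 1.30.

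The strictest case is Bonferroni over all 16, 0.05/16 = 0.0031 per test. With 36 per group (45 less an assumed 20% loss), t-test power is 99.4% for IFN-γ and 99.2% for TNF-α. With 45 per group it exceeds 99.9% for both (normal approximation).

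**Cost for modest effects.** Smallest standardised difference detectable with 80% power at 45 per group (t-test): 0.60 at 0.05, 0.66 at 0.025 and 0.82 at 0.05/16. In sample-size terms the last step is (0.82/0.60)² ≈ 1.9-fold.

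**The case against.** Several points on the other side have force.

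- **A reader might infer that a false primary finding is more likely than not.** The article does not support that. It needs every null to be true and a correlation below about 0.24. TNF, IFN-γ and IL-10 are each measured as transcript and as protein at the same time point, so independence is implausible. The plan also expects real IFN-γ and TNF differences, which reduces the number of true nulls. The 56% is an upper bound for 16 tests, not an expected rate.
- **That each marker gets its own decision test is inferred.** The section assigns t-tests or Mann-Whitney tests to patient characteristics and correlations to primary-outcome variables. It never says that one p ≤ 0.05 makes the primary outcome positive. The threshold sentence nevertheless has no limit and covers any such comparison.
- **The trypanocidal claim is little affected.** Two tests give at most 9.75%. Counting only false reductions, the rate is 1 − 0.975² = 4.9%. This stands: the inflation sits in the inflammatory panel.
- **The study is observational, calls itself exploratory, and an unseen analysis plan may handle multiplicity.** Silence alone would not be a finding. Here, though, the Methods name a primary outcome, power it at 0.05 and state an unqualified significance rule. A single word in the Discussion does not limit how those p-values are read. The mismatch over parasitic load lies within the article itself.
- **Making IFN-γ and TNF the only primary markers would drop serological reactivity**, which the main objective names first. This is right, and the fix below avoids it.

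**Conclusion.** The point holds in a limited form. Following the stated rule across 16 primary markers gives a chance of at least one false primary finding of 26% to 56% for assumed correlations from 0.7 down to 0, against a nominal 5%. Even at 0.9 it is about 15%. These figures assume a between-group test of each marker at 0.05 and no effect on any of them. The inflammatory panel drives the excess; the trypanocidal pair adds little. Separately, and without any assumption, the abstract and the design section disagree on whether parasitic load is primary. The plan should be changed on both counts, but neither affects recruitment or sampling.

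**What to change.** In the Statistical analysis section, make the two Table 1 domains separate primary families and control error within each.

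1. **Immunomodulatory family.** Serum IFN-γ and TNF, the markers that sized the study, are lead markers tested with Holm (smaller p against 0.025; if it passes, the larger against 0.05). The remaining 12 inflammatory markers (13 if nitrate and nitrite are separate) are tested with Benjamini-Hochberg at a 5% false discovery rate and reported as supporting the lead result.
2. **Trypanocidal family.** Antibody reactivity and parasite load are tested with Holm, so both stay primary.
3. **One list.** Give the same primary markers, including the status of parasitic load, in the abstract, design section and Table 1, and name the between-group test used for them.

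If the marker comparisons are meant to be exploratory only, the section should say so where it sets the threshold.

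The cost is wording, plus a dated record of the change because recruitment opened in March 2023. No extra samples or patients are needed. Power for modest differences falls: at 45 per group the detectable difference rises from 0.60 to 0.66 at the first Holm step, and would reach 0.82 under full Bonferroni over 16. Separate families also leave up to 1 − 0.95² = 9.75% across the two domain claims, which is acceptable if each domain is reported as its own question.
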